#### **Statistical Interim Analysis, Data Review and Stopping guidelines**

Registration and assessment data are captured online via Qualtrics. Participants are assigned a unique code for all data files and audio tapes. Access to the system is restricted to named study personnel and via password protection. The University of Oxford's (UO) IT services have arranged for the files to be encrypted and backed up on a weekly basis. The data are copied to separate tapes, that are inaccessible without the TSM database by the UO IT Services. Papers from clinical interviews are kept in locked cabinets at UO. The audiotapes from clinical interviews are backed up online with password-protection and access restricted to study personnel. The blood samples are centrifuged as soon as the laboratory at the University of Surrey receives them on the day of collection. Saliva samples are analysed at the University of Surrey by RIA analysis.

In line with the OCTRU and the Medicines for Human Use Clinical Trials Regulations (2004), we have not recruited a Data Monitoring Committee because recruitment and follow-up occur over a short period, there are minimal risks to participants and the trial protocol is not modified regardless of any interim data. No interim analyses are planned.

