#### **Timing of Final Analysis**

Originally, as stated in the published trial protocol ([name] et al., 2018), we had planned to analyse the trial data once the trial was finished at two year follow-up. However, the outbreak of the Covid pandemic may have added additional risk to the mental health of emergency workers and therefore, if iCT-R leads to improvement in emergency workers' mental health compared to Mind-Online or Standard Treatment, it would be beneficial to roll out the intervention as soon as possible. It has been discussed and agreed with the Trial Steering Committee that data could be analysed early, namely after completion of the 1-year follow-up period, if rates of PTSD and MDD diagnoses in the total sample at 1-year follow-up are higher than expected. At 1 year follow-up, in the total sample, rates of PTSD are 8.7% compared to 8.3% in non-intervention studies of this population [1] and the general population rate of 3%. Rates of depression are 15.8% compared to 10.6% in non-intervention longitudinal studies of this population [1] and the general population rate of 10.3%. Since

there are higher than expected rates of PTSD and MDD diagnoses at 1-year follow-up in the total sample we now plan to analyse data at 1-year follow-up. Two-year follow-up data (including sub-thresholds) will be analysed by including them into the 1-year outcome models once they have been completed.

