## **Statistical Analysis Outline**

Linear and logistic mixed effects modelling are used to test the primary and secondary trial objectives (with the exclusion of the health economic analyses, which will be conducted by [name] and therefore not part of this analysis plan, as well as the hormone and immune function analyses which will be conducted by Professors [name] and [name]), which is the standard technique for analysing clinical trials.

For the primary and secondary trial objectives, 1-year follow-up is the short-term primary outcome time point (except for immune and hormone function for which the time-point is post-intervention), PTSD and MDD diagnoses are the primary outcome measures. Once completed, the 2-year PTSD and MDD diagnoses at 2-year follow-up are the long-term and main primary outcome time points.

Both repeated assessments and intervention arm are specified as categorical variables for reasons of flexibility in the modelling approach. Repeated assessments, intervention arm, their interaction effects, and baseline scores and covariates are estimated as fixed effects and random effects are estimated for time (level 1) nested within the participants (level 2). An unstructured variance-covariance matrix is used to model the error correlation structure within the participants.

Global comparisons for the main effect of intervention group and the interaction effects between time and intervention group are tested for primary and secondary trial objectives and further group comparisons are carried out if the global comparisons are significant. The hierarchy of the group comparisons reads as follows: 1) iCT-R versus Mind-Online, 2) iCT-R versus Standard Practice, and 3) Mind-Online versus Standard Practice. Site is introduced as a random effect in the analyses of the primary trial objectives. If non-significant, site will not be carried forward into further trial analyses.

Maximum Likelihood estimation is used. Assumptions for mixed effects modelling are tested and normality of residuals are confirmed for the outcome measures. If assumptions are violated, resampling approaches will be used.

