## **STATISTICAL PRINCIPLES**

### **Statistical Significance and Multiple Testing**

In the case of different scaling, continuous variables are standardized for the analysis. Global comparisons are tested and if significant, group comparisons are then carried out.

[name], [name], [name], [name], [name], [name], [name], [name], [name], [name], [name], & [name] Cognitive resilience training to prevent PTSD and MDD in paramedics: A randomised controlled trial.

If not specified otherwise, one or the other, main effects of intervention group or interaction effects between intervention group and time in favour of iCT-R, indicate intervention superiority.

All analyses will be carried out with a significance level of  $p < .05$ , two-sided.

No adjustments for multiple testing are made, as the primary trial objective is to evaluate any superiority in efficacy of the new resilience intervention compared to the existing online intervention (group comparison between these two groups of highest priority and directive hypothesis).

Confidence intervals are reported at the 95% level, two-sided.

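### The SAP adds an unadjusted 1-year efficacy test ahead of the main 2-year primary and does not recognise it as an interim analysis

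*Combined protocol and SAP*

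**What the plan says.** SAP 3.5 (Timing of Final Analysis) explains that analysis had been planned for the end of the 2-year follow-up. It brings the analysis forward because "there are higher than expected rates of PTSD and MDD diagnoses at 1-year follow-up in the total sample we now plan to analyse data" at that point. The motive given is that, if iCT-R helps, "it would be beneficial to roll out the intervention as soon as possible".

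SAP 3.7 (Statistical Analysis Outline) gives both time points primary status. It says that "1-year follow-up is the short-term primary outcome time point" and that, once complete, "the 2-year PTSD and MDD diagnoses at 2-year follow-up are the long-term and main primary outcome time points". On the outcome it says "PTSD and MDD diagnoses are the primary outcome measures". SAP 6.1 repeats the two-stage arrangement.

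SAP 4.1 runs all analyses "with a significance level of $p < .05$ , two-sided", and adds: "No adjustments for multiple testing are made, as the primary trial objective is to evaluate any superiority in efficacy of the new resilience intervention". It also accepts either a main effect of group or a group-by-time interaction favouring iCT-R as evidence of superiority. SAP 3.7 and 6.2 allow pairwise contrasts only after a significant three-arm global test, in a fixed order that starts with iCT-R versus Mind-Online.

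SAP 3.4 nevertheless states: "No interim analyses are planned". Protocol 11.1.1 says the same.

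**The concern.** A between-arm efficacy comparison made before the main endpoint is complete, with a possible action attached, is an interim efficacy analysis whatever it is called. The plan gives it the same 5% threshold as the later analysis and sets no rule for how the two results combine into a claim. A success statement could rest on 1 year or on 2 years, possibly on either diagnosis, and on either of two model terms.

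The reason in SAP 4.1 is that one group contrast has priority. Together with the global test and the ordered contrasts, that deals with having three arms. Nothing in the plan deals with the other sources of multiplicity. At stake is a claim for iCT-R, and perhaps its roll-out, made at a higher false-positive rate than the stated 5% suggests.

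**Working it through.** **1. What the sample size was built for.** Inputs from protocol 11.2: 25% versus 12.5%, two-sided 0.05, 80% power. With p̄ = 0.1875:

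n per arm = [1.960·√(2·0.1875·0.8125) + 0.842·√(0.25·0.75 + 0.125·0.875)]² / 0.125² = 151.9, so 152.

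Then 2 × 152 = 304, 3 × 152 = 456 and 456/0.8 = 570. The odds ratio is (0.125/0.875)/(0.25/0.75) = 0.429. The plan's figures are reproduced, and they describe one test of one outcome at 0.05.

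**2. Number of primary tests of iCT-R versus Mind-Online.** There are two time points. There are two diagnoses if PTSD and MDD are modelled separately, one if combined. If independent and with no preceding global test:
- four tests: 1 − 0.95⁴ = 18.5%
- two tests: 1 − 0.95² = 9.75%

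**3. Allowing for correlation and the global test.** The 1-year data are reused at 2 years, so the tests are correlated. The documents give no correlations. I assumed 0.3–0.7 between time points and 0.3–0.5 between diagnoses, with the product of the two across both. Normal test statistics were simulated for three arms with iCT-R equal to Mind-Online. A pairwise claim needed a global statistic above the 5% point of chi-square on 2 df, and |z| > 1.96 for the pair. Standard Practice was either equal to the other arms, or different by the planned effect (z = 2.8), in which case the global test nearly always passes.

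| iCT-R vs Mind-Online, false positive at either time point | Two-sided | In favour of iCT-R |
|---|---|---|
| One test, for reference | 5% | 2.5% |
| Two diagnoses, Standard Practice differs | 14.7–17.5% | 7.4–8.9% |
| Two diagnoses, all arms equal | 7.9–9.2% | 4.0–4.6% |
| One combined outcome, Standard Practice differs | about 8–9.5% | about 4–5% |
| One combined outcome, all arms equal | 4.3–4.8% | about half of that |

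**4. Adding the either-effect rule.** Each analysis was given both a main effect and an interaction. The first used post-intervention and 1 year; the second added 2 years. With two diagnoses, all arms equal, the global test required and the same correlations, the risk is 12.4–13.5% two-sided and 6.4–7.0% in favour of iCT-R. This rule was not simulated for a combined outcome.

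**5. One outcome or two?** The SAP does not settle it. For two: SAP 3.5 gives separate PTSD and MDD rates, and SAP 6.2 refers to outcomes and models in the plural. For one: SAP 6.1 speaks of a single primary measure, SAP 6.2 separates the conditions explicitly for symptom severity but not for diagnoses, and the planning rate in protocol 11.2 combines the conditions.

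**The case against.** The strongest reply is that the SAP is open about the change. It explains why the analysis was moved, records the Trial Steering Committee's agreement, ranks 2 years as the main time point, and requires a global test before any pairwise claim. The decision to look early used total-sample rates, which do not by themselves reveal arm differences. All of that stands. But a ranking is not an error-control rule: nothing in the SAP says that a positive 1-year result is provisional.

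A reader might infer more than the documents support, in three ways.

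- **That 15–18% is the trial's error rate.** It applies only if the diagnoses are tested separately and the global test gives little protection because Standard Practice differs. With a combined outcome and all arms equal, the risk before the either-effect rule does not exceed 5%.
- **That the reason for looking early was empty.** PTSD at 8.7% against 8.3% is a negligible excess. MDD at 15.8% against 10.6% is not: z is about 3.0 at an assumed n = 456, since SAP 3.5 gives no denominator. In any case the inflation comes from testing the arms twice, not from the trigger.
- **That the 2-year assessments are compromised.** SAP 3.2 has interviews done by an independent assessor blind to allocation and questionnaires completed without researcher involvement. Group-level results do not disclose anyone's arm. Protocol 9.4 offers iCT-R to Standard Practice participants at 104 weeks. The documents do not show harm here, and an embargo on 1-year results would defeat the purpose of the early analysis.

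**Conclusion.** The point holds as a design inconsistency. An interim efficacy analysis has been added, is not recognised as one, and carries full alpha alongside the main analysis, with a no-adjustment reason that covers only the arms.

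The size depends on facts the SAP leaves open. With separate diagnoses, the two-sided risk for the priority contrast is about 15–18% if Standard Practice differs and about 8–9% if all arms are equal, the latter rising to about 12–13.5% (6–7% in favour of iCT-R, against 2.5%) under the either-effect rule. With a combined outcome it is about 8–9.5% or about 5% respectively, before that rule. Every figure rests on the assumed correlations. The case for correcting the SAP rests on the inconsistency, not on the top of the range.

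**What to change.** In SAP 3.4, 3.5 and 4.1:

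- Replace the no-interim statement. Call the 1-year arm comparison an interim analysis and label it non-confirmatory.
- Name the 2-year iCT-R versus Mind-Online contrast as the only confirmatory test, at two-sided 0.05. Naming one contrast also closes the main-effect-or-interaction route to a claim.
- State the diagnosis outcome for that test: PTSD or MDD combined, or both separately with Holm.

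The main cost is that a positive 1-year result can be reported only as provisional. Power at 2 years is unchanged with a combined outcome. Under Holm it is somewhat lower per diagnosis: the first step is at 0.025, where 152 per arm gives about 71% at the planning rates of 25% versus 12.5%. Those rates are combined and include subsyndromal cases, so 71% only illustrates the loss.

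If the sponsor wants a confirmatory claim at 1 year, alpha must be split across the two time points and the power restated for each.

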## **Definition of Analysis Populations**

The analysis population is intent-to-treat (ITT). All participants in the randomised groups are analysed. In addition, a complier-average causal effect analysis (CACE) will be conducted to test any influence of compliance on the intent-to-treat intervention effect of the primary trial objectives/ analyses. CACE is then compared with the intent-to-treat intervention effects resulting from the primary analyses and results are reported.

## **TRIAL POPULATION AND DESCRIPTIVE ANALYSES**

### **Representativeness of Study Sample and Patient Throughout**

Paramedic students aged 18 and above in the years 1, 2 or 3 of their paramedic training programme are eligible for the study. They are screened for levels of PTSD and MD, and a trained research assistant under supervision of the Principal Investigator will contact participants if they score in the clinical range on measures of PTSD or MD, or report suicidal ideation to evaluate whether they are eligible or need treatment. Participants will be excluded from the study if their symptoms are interfering with their lives and they would like treatment, and the research assistant will then offer information on evidence-based treatment in their local area.

The flow chart of participants through each stage of the trial, including numbers of participants randomly assigned, receiving the intervention, completing the study protocol, and analysed for the primary outcome is provided following current CONSORT guidelines.

Protocol violations or deviations and information relating to the screening data including potential numbers of ineligible patients randomised, together with reasons, are also described.

#### **Withdrawal from treatment and/or follow-up**

Number and percentage of participants who have withdrawn from the trial intervention will be summarised across intervention arms and for each intervention arm, together with reasons for withdrawal if available.

Numbers and percentage of participants lost to follow-up across intervention arms and within each intervention arm are also reported.

In addition, numbers of participants who have withdrawn or have been lost to follow-up are reported in the CONSORT flow chart.

#### **Baseline Comparability of Randomised Groups**

Total sample size and group sizes (iCT-R, Mind-Online, Standard Practice), means, standard deviations, frequencies at baseline for the groups and the total sample, and occurrence of missing data and loss to follow-up for the groups, for any compliance groups, and the total sample are reported.

#### **Unblinding**

All cases unblinded to blinded assessors are reported and summarised (absolute numbers and percentages).

#### **Description of Compliance with Intervention**

Level of compliance will be defined as 1) number of online modules completed during the intervention, 2) practice of tools.

A complier-average causal effect analysis (CACE) is used to test any influence of compliance on the intent-to-treat intervention effect of the primary trial objective analyses.

1067

1068

1069 **Reliability**

1070           The primary outcome measures, such as Structured Interviews by clinicians and self-  
1071 reports for the primary outcomes and nearly all of the secondary outcome measures are  
1072 standard instruments that have been validated and have shown good reliability.

1073           Scoring is done as described in the manuals or publications for the measures and  
1074 relevant sub-scales and Cronbach's Alphas are reported for the study sample.

1075           Interrater-reliability is reported for 1-year follow-up data. 10% of diagnoses at 1-year  
1076 follow-up are rated by a second rater.

1077           To ensure consistency in the data, validation checks on the data are carried out before  
1078 locking the dataset and analysis of the data. These include checking for potential data entry  
1079 mistakes, duplicate records, checking the range of variable values, missing data value codes,  
1080 etc.

1081 **ANALYSIS**

1082 **Outcome Definitions**

1083 Outcome measures:

1084           The primary outcome measure for the primary trial objective is PTSD and MDD  
1085 diagnoses (SCID-5;). Secondary outcomes with regards to the primary trial objective are  
1086 PTSD symptom severity (PCL-5) and MDD symptom severity (PHQ-9).

1087

1088           Outcome measures for the secondary trial objectives include resilience measures  
1089 (Wagnild-Resilience Scale and CD-RISC, both continuous), well-being measures (subscale  
1090 rumination of the RIQ, GAD-7, GHQ-12, WEMWBS), general health measures (weight and  
1091 height; Insomnia severity index; Smoking Behaviour Questionnaire, sum score for both  
1092 items; Alcohol Use Questionnaire, unit increase/ decrease/ stayed the same), health economic  
1093 costs (intervention costs per QALY gained based on 4 measures), and hormone and immune  
1094 function (collected with saliva samples and CRP plasma).

Measures to test the tertiary trial objective are risk factors and predictors at baseline, such as level of social support (adapted from a brief measure of social support), trauma exposure (trauma screener), demographic data (general information questionnaire), neuroticism as a personality factor (subscale neuroticism from the Eysenck Personality Questionnaire), level of concrete thinking (CAT), and frequency, duration, and distress with regards to intrusive memories (Intrusions Questionnaire).

More information on the outcome measures can be found in the published trial protocol ([name] et al., 2018).

Time points:

Data are collected at pre-intervention, post-intervention, at 6-months follow-up, at 1-year follow-up and at 2-years follow-up. PTSD and MDD diagnoses are assessed pre-intervention, post-intervention, at 1-year and at 2-years follow-up, PTSD and MDD symptom severity are assessed at all measurement points. Secondary outcome measures are assessed at pre-intervention, post-intervention, and at 1-year and at 2-years follow-up. All measures for the tertiary trial objective are assessed at pre-intervention, at 1-year and at 2-years follow-up. All tertiary measures (except for demographics) are assessed at post-intervention, and trauma exposure, concrete thinking and intrusion measures are collected at 6-months follow-up, as well.

For the early analysis of the trial results, 1-year follow-up is the short-term primary outcome time point. Once the trial has been completed, the primary outcome time point is 2-years follow-up as described in the published trial protocol.

## **Analysis Methods**

Analyses of the primary trial objectives:

To analyse any differences between the intervention arms in terms of effectiveness with regards to rates of PTSD and MDD diagnoses (SCID-5) at 1-year follow-up (short-term primary outcome time point) and at 2-years follow-up (long-term primary outcome time point once completed), intervention condition and the interaction between intervention time and

intervention group on rates of PTSD and MDD diagnoses, logistic mixed effects models with PTSD and MDD diagnoses as outcomes (short-term outcome 1-year follow-up data, long-term outcome 2-years follow-up once completed) are specified and analysed.

To analyse any differences between the intervention arms in terms of effectiveness with regards to PTSD symptom severity (PCL-5) or MDD symptom severity (PHQ-9) at 1-year follow-up (short-term primary outcome time point) and at 2-years follow-up (long-term primary outcome time point once completed), intervention condition (categorical; iCT-R versus Mind-Online versus Standard practice; level 2) and the interaction between intervention time (categorical; post-intervention, 6-months follow-up; 1-year-follow-up, 2-year follow-up, once completed; level 1) and intervention group on PTSD or MDD symptom severity, linear mixed effects models with either PTSD or MDD symptom severity as outcomes are specified and analysed.

Both repeated assessments and intervention arm are specified as categorical variables for reasons of flexibility in the modelling approach. Repeated assessments/ time, intervention arm, both their interaction effects, and baseline scores and covariates are estimated as fixed effects and random effects are estimated for time (level 1) nested within the participants (level 2). An unstructured variance-covariance matrix is used to model the error correlation structure within the participants. Estimation method is Maximum Likelihood. Normality of the residuals for the outcomes is confirmed visually.

Randomisation has been done by stratification by site, gender, and baseline PTSD symptom severity and MDD symptom severity. Therefore, baseline PTSD symptom severity and MDD symptom severity and randomisation factors are added as covariates in these models. Site is added as random factor in those models. If non-significant, they will not be carried forward into further analyses.

In case of a significant main effect of intervention group or interaction effect between intervention group and time with regards to the primary outcome measure (PTSD and MDD diagnoses) and secondary outcome measures for the primary trial objective (PTSD and MDD symptom severity), intervention group comparisons are carried out using pairwise contrasts. iCT-R (coded as '1') is tested against Mind-Online (coded as '0') and a significant main effect or interaction in favour of iCT-R indicates intervention superiority (comparison of highest priority) of the newly developed resilience intervention over the existing online intervention. In a second step, iCT-R (coded as '1') is then tested against Standard Practice

(coded as '0') and again, a significant main effect or interaction in favour of iCT-R indicates intervention superiority for the newly developed intervention over usual Standard Practice. In a third step, Mind-Online (coded as '1') is tested against Standard Practice (coded as '0') and a significant main effect or interaction in favour of Mind-Online indicates intervention superiority of the existing online intervention compared to Standard Practice.

Adjusted/ estimated mean differences and Cohen's d's with standard deviation at baseline in the denominator are reported in tables for continuous outcomes for the intervention effects from results of linear mixed effects models and frequencies of diagnoses (absolute numbers and percentages) and absolute values as well as estimated/ adjusted odds ratios are reported for dichotomous outcomes.

All significance tests are carried out on a  $p < .05$  level, two-sided, and confidence intervals are reported on the 95% level.

Analyses of secondary trial objectives:

Any intervention effects on the secondary outcome measures, such as resilience (Connor-Davidson Resilience Scale,; Wagnild Resilience Scale), rumination (ruminative responses brooding subscale; Responses to Intrusions Questionnaire rumination subscale), anxiety (GAD-7), Smoking Behaviour (Smoking Behaviour Questionnaire), Alcohol consumption (Alcohol Use Questionnaire), psychological distress (GHQ), well-being (Warwick Edinburgh Mental Wellbeing Scale), sleep quality (Insomnia severity index), and weight, are analysed for the short-term primary outcome time point of 1-year and for the long-term primary outcome time point of 2-years follow-up, once completed.

Linear mixed effects models are specified for these continuous outcome measures. Intervention condition (categorical; iCT-R versus Mind-Online versus Standard Practice; level 2) and the interaction between intervention time (categorical; post-intervention, 1-year-follow-up, 2-years-follow-up once completed; level 1) are specified as fixed effects predictors in the models.

Baseline values for the respective secondary outcome are added as covariate in these models together with PTSD and MDD symptom severity at baseline, and randomisation factors.

Adjusted/ estimated mean differences and Cohen's d's with standard deviation at baseline in the denominator are reported in tables for continuous outcomes for the intervention effects from results of linear mixed effects models.

The health economic analyses will be conducted and reported by [name] and and hormone and immune function are tested by collaborators and are therefore not part of this statistical analysis plan. A plan for the health economic and hormone and immune function analyses will be agreed.

Analyses of the tertiary trial objectives:

In order to investigate whether risk factors and predictors at baseline, such as level of social support, trauma exposure, demographic data, past and current comorbidities, neuroticism as a personality factor, level of concrete thinking, and frequency/ duration/ distress with regards to intrusive memories, influence any iCT-R intervention effects on PTSD or MDD diagnoses, psychological distress, and well-being at 1-year follow-up, a mixed effects model for each of the outcomes, PTSD and MDD diagnoses, psychological distress, and well-being, is specified with baseline scores of PTSD or MDD symptom severity or psychological distress or well-being as covariate. The main effects of the respective baseline predictors (time-invariant covariates) and the two-way interactions between each of those baseline predictors and time (categorical: post-intervention, 1-year follow-up; level 1) will be analysed.

Again, Maximum Likelihood is used if the assumption of normality of the residuals of the outcomes is fulfilled. An unstructured variance-covariance structure matrix is used, all significance tests are carried out on a  $p < .05$  level, two-sided, and confidence intervals are reported at the 95% level.

In case of any significant interaction effects between time and baseline moderators, simple slope analyses are carried out to investigate the direction of any moderation effects.

Further tertiary trial objectives to investigate whether changes (decrease) in process measures, such as rumination, intrusive memories, and increases in concrete thinking, from baseline to post-intervention in the iCT-R condition predict lack of PTSD or MDD diagnoses

[name], [name], [name], [name], [name], [name], [name], [name], [name], [name], [name], & [name] Cognitive resilience training to prevent PTSD and MDD in paramedics: A randomised controlled trial.

(versus presence of PTSD or MDD diagnoses) at 1-year follow-up are analysed using logistic regressions with difference scores from pre to post for the process measures and baseline scores of PTSD or MDD symptom severity as covariate.

CACE analysis:

A complier-average causal effect analysis (CACE) is used to test the influence of compliance on the intent-to-treat intervention effect of the primary trial objectives/ analyses. Magnitude of compliance will be defined as 1) number of online modules completed during the intervention, and 2) practice of tools. Based on these variables, trajectories of compliance are determined. CACE will then be compared with the intent-to-treat intervention effects resulting from the primary analyses and the results will be reported.

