### 11.2 The Number of Participants

We plan to recruit 570 participants.

The risk of student paramedics developing full syndromal PTSD and MD over two years without intervention is 10% (1), and 25% if subsyndromal PTSD and MD that cause significant distress are included. We predict that our intervention will reduce the relative risk by 50%. Setting power at 80%,  $\alpha=.05$  and hypothesizing a reduction of relative risk of 50% gives an odds ratio of 0.429, which requires a total sample size of N=304 to show a risk reduction of 50% between the active and placebo intervention. Thus, each condition would require N=152. Since we have a third condition (no-training control), the total sample size required would be N=456. Allowing for a 20% rate of attrition, we will require a total sample size of N=570.

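### The linear mixed models give the baseline score one slope for all visits; if its relation to outcome weakens over time, 2-year contrasts on PCL-5, PHQ-9 and the continuous secondary outcomes lose some precision

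*Combined protocol and SAP*

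**What the plan says.** The SAP describes the model twice in nearly the same terms. Under Statistical Analysis Outline: "Repeated assessments, intervention arm, their interaction effects, and baseline scores and covariates are estimated as fixed effects". Under Analysis Methods, for the primary objectives: "Repeated assessments/ time, intervention arm, both their interaction effects, and baseline scores and covariates are estimated as fixed effects". Both sections make time and arm categorical, for flexibility, and use an unstructured within-participant covariance.

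The PCL-5 and PHQ-9 models cover post-intervention, 6 months, 1 year and 2 years, and carry baseline PTSD and depression severity as covariates. The other secondary outcomes have no 6-month visit. For them the SAP adds: "Baseline values for the respective secondary outcome are added as covariate in these models", alongside baseline PTSD and depression severity.

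The tertiary moderator models differ. There the SAP explicitly lists two-way interactions between each baseline predictor and time.

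**The concern.** A baseline score entered only as a main effect has the same slope at 6 weeks as at 2 years. In a trial this long, a baseline score could well predict an early visit better than a late one. A single fitted slope is then a compromise. Maximum likelihood pulls it towards the visits that baseline predicts best, because their residual variance is smallest. If those are the early visits, the slope is too steep at 2 years and part of the benefit of adjustment is lost there.

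What is at stake is efficiency at the time point the SAP treats as the long-term main one. The restriction also sits oddly with the freedom given to time, arm and covariance, and the SAP gives no reason for it.

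**Working it through.** **1. Reading of the text.** In both descriptions the interaction phrase refers to time and arm. No baseline-by-time term is listed for the primary or secondary models, whereas the tertiary models name one. As written, the slope is common to all visits.

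**2. The plan's own figure.** Protocol section 11.2 takes a two-year risk of "25% if subsyndromal PTSD and MD that cause significant distress are included", halved to 12.5%: "hypothesizing a reduction of relative risk of 50% gives an odds ratio of 0.429". Check: (0.125/0.875)/(0.25/0.75) = 0.429. With two-sided alpha 0.05, 80% power, pooled variance and no continuity correction:

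n = [1.960·√(2·0.1875·0.8125) + 0.842·√(0.25·0.75 + 0.125·0.875)]² / 0.125² = (1.082 + 0.459)²/0.015625 ≈ 152.

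This agrees with "each condition would require N=152". Then 3 × 152 = 456 and 456/0.8 = 570. It is an unadjusted comparison of two proportions, so the baseline term does not enter it.

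**3. Formula for the continuous outcomes.** With randomised arms and complete data, the variance of the arm contrast at visit t is proportional to Var(Y_t − bX). With unit variances the visit's own best slope is its correlation with baseline, ρ_t. Relative to that slope, a common slope b inflates the variance by

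(b − ρ_t)² / (1 − ρ_t²).

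The common slope solves b = 1′S⁻¹ρ / 1′S⁻¹1, where S is the covariance of Y − bX. It was iterated to convergence, which gives the maximum likelihood value under an unstructured covariance.

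**4. Assumed inputs.** The documents give no SDs or correlations. All the correlations below are assumptions, with four visits and complete data.

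**5. Worked case.** Baseline correlations 0.7, 0.6, 0.5, 0.4; between-visit correlation 0.60 throughout. The common slope is b = 0.629.
- 6 weeks: (0.629 − 0.7)²/0.51 = 1.0%
- 6 months: (0.629 − 0.6)²/0.64 = 0.1%
- 1 year: (0.629 − 0.5)²/0.75 = 2.2%
- 2 years: (0.629 − 0.4)²/0.84 = 6.2%

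**6. Range: variance inflation at 2 years.**

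| Baseline correlation at 6 wk / 6 mo / 1 yr / 2 yr | Between-visit 0.55 | Between-visit 0.60 | Falling with lag: 0.70, 0.60, 0.50 |
|---|---|---|---|
| 0.50 at every visit | 0 | 0 | 0 |
| 0.50 / 0.47 / 0.43 / 0.40 | 0.4% | 0.4% | 0.4% |
| 0.60 / 0.55 / 0.50 / 0.45 | 1.0% | 1.1% | 1.0% |
| 0.70 / 0.60 / 0.50 / 0.40 | 5.7% | 6.2% | 5.1% |
| 0.70 / 0.55 / 0.45 / 0.30 | 11.0% | 12.3% | 9.6% |

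If between-visit correlations fall faster (0.75, 0.60, 0.45), the last two rows become 4.7% and 8.9%. In the steepest row the 2-year variance under the common slope is 1.00 to 1.02 times the unadjusted variance, so adjustment then gains nothing at that visit. Rising SDs reduce the loss: for 0.70/0.55/0.42/0.30 with between-visit correlation 0.60, it is 12.2% with equal SDs and 6.3% if SDs rise from 1.0 to 1.3.

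**7. In power terms.** A contrast with 80% power under visit-specific slopes has power Φ(2.80/√(variance ratio) − 1.96). That is 79.6% at a ratio of 1.011, 77.6% at 1.062 and 75.3% at 1.123.

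**8. Three-visit outcomes.** With between-visit correlation 0.60, the 2-year loss is 0.8% for 0.60/0.50/0.45, 4.9% for 0.70/0.50/0.40 and 10.4% for 0.70/0.45/0.30.

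**9. Binary outcome.** A simulation of 600 trials (152 per arm, three visits, log-odds slopes 1.3, 0.8 and 0.4, logistic GEE standing in for the logistic mixed model) gave a 2-year standard error of 0.355 with a common slope and 0.337 with visit-specific slopes. Power was 80.0% and 82.2%, each with Monte Carlo error of about 1.6 points, and 80.8% with no baseline term.

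**The case against.** The best reply is that a main-effect baseline covariate is a legitimate and simpler specification, and that every loss above depends on correlations the documents do not report. Both points stand. A starting correlation of 0.7 may also be high: volunteers whose symptoms interfere with their lives and who want treatment are excluded, which may narrow the baseline range. Under shallow falls the loss is about 1% of variance or less.

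Three stronger readings are tempting but not supported.
- *That 2 years is necessarily the worst-served visit.* With correlations of 0.45 at 6 weeks and 0.50 afterwards, the loss is 0.2% at 6 weeks and near zero at 2 years.
- *That the primary analysis or its 152 per arm is weakened by these percentages.* The primary outcome is SCID diagnosis in a logistic mixed model. Covariate adjustment there does not act simply as variance reduction, and the simulated difference was small. PCL-5 and PHQ-9 are secondary measures under the SAP's Outcome Definitions.
- *That the contrast is biased once data are missing.* This needs unequal slopes together with dropout that depends on baseline severity differently in each arm. One assumed scenario of that kind, with about 20% dropout, gave a spurious difference of only 0.02 to 0.03 SD. Nothing in the documents points to such dropout, and the SAP's Sensitivity Analysis section already plans models with predictors of missingness, and imputation.

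**Conclusion.** The point holds as a conditional efficiency gain for PCL-5, PHQ-9 and the continuous secondary outcomes. The SAP does specify a common baseline slope. If slopes are equal across visits, nothing is lost. If the relation to baseline weakens by 2 years, the 2-year variance is larger by about 0.4 to 1% for a shallow fall, 5 to 6% for correlations falling from 0.7 to 0.4, and 10 to 12% for a fall from 0.7 to 0.3. The limits move by about a point with the between-visit correlations assumed, and the loss is smaller if SDs rise over time. These figures rest on assumed correlations and complete data.

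It is not a validity error: randomisation keeps the linear contrast unbiased with complete data. The planned 570 is unaffected. The case for acting is that the possible gain at 2 years comes at almost no price.

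**What to change.** In Statistical Analysis Outline and Analysis Methods, add to the linear mixed models for PCL-5, PHQ-9 and the continuous secondary outcomes a fixed effect for the outcome's own baseline score by categorical time. The other baseline scores and the randomisation factors can stay as main effects. For SCID diagnoses no change is needed on this ground.

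The cost is three extra parameters per baseline score so treated with four follow-up visits, or two with three visits, which is negligible with several hundred participants. It is a change of SAP wording and model code only, with no new data and no change to sample size. It should be fixed before the outcome data are compared by arm.
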